## Abstract

**Background:**

As the survival rate of preterm infants continues to rise worldwide, more infants are at risk of developing sight-threatening retinopathy of prematurity (ROP). Destructive retinal laser treatment and intravitreal injections of anti-vascular endothelial growth factor (VEGF), factor, which have potential systemic side effects, are necessary to prevent blindness in severe cases of ROP. Off-label use in clinical settings suggests that dexamethasone eye drops, 1 mg/ml, may prevent the progression of ROP to severe disease (Type 1 ROP) requiring treatment. Our current study aims to assess the efficacy and safety of timely administered dexamethasone eye drops to reduce the need for laser or anti-VEGF ROP treatment in preterm infants.

**Methods:**

In a randomized prospective interventional, multi-centre, double-blinded trial, we plan to include 100 infants with severe ROP born before gestational age 30 weeks in Sweden. Infants will be randomized to intervention with dexamethasone eye drops (1 mg/ml) *(n* = 50) or placebo, saline (*n* = 50) until either ROP is resolved or severe ROP (Type 1 ROP) development occurs, fulfilling ROP treatment criteria. Eye drops will be administered one drop per day or every other day, depending on the severity of ROP, with a maximum duration of 12 weeks. The primary objective is to evaluate whether dexamethasone intervention reduces the proportion of infants developing Type 1 ROP compared to infants receiving a placebo. Adverse events and potential side effects will be recorded, such as high intraocular pressure and growth restriction. Levels of cortisol in saliva and glucose in urine will be measured repeatedly. Secondary outcomes will include the timing of ROP progression, the recurrence rate after ROP treatment and retinal morphology. An ophthalmological follow-up will be initiated at 2 and 5.5 years of age, evaluating visual acuity, refractive errors, strabismus, retinal morphology and ophthalmological complications. All outcomes in the study will be compared between the infants receiving dexamethasone intervention and those receiving placebo.

**Discussion:**

Timely administration of dexamethasone eye drops may prevent severe ROP from progressing to Type 1 ROP, which requires treatment. This study aims to assess the efficacy and safety of dexamethasone intervention to support its clinical use and national guidelines.

**Trial registration:**

EudraCT, 2020–004933-19, registered in January 2021 and CTIS, 2023–505318-97–00, registered in August 2023.

**Clinical trial number:**

Not applicable.

**Supplementary Information:**

The online version contains supplementary material available at 10.1186/s12887-025-05673-x.

## Background

Advancements in neonatal care have improved survival rates of preterm infants worldwide, leading to a growing number of infants suffering preterm-related morbidities [1–3]. Retinopathy of prematurity (ROP) is one of the leading causes of childhood blindness worldwide and primarily affects extremely preterm infants [4, 5].

In the initial phase of ROP, which occurs shortly after birth, blood vessel development in the retina is halted. During the next several weeks to months, the peripheral neural retina develops slowly and remains avascular. Increasing ischemia and inflammation in the avascular retina can lead to pathological neovascularization driven mainly by vascular endothelial growth factor (VEGF). In the worst-case scenarios, this neovascularisation leads to retinal detachment and blindness [6–8]. About 5–10% of ROP cases are severe enough to require treatment with retinal laser photocoagulation and/or with intravitreal anti-VEGF injections [4]. International guidelines regulate treatment indications based on ROP classification [9]. ROP is classified into ROP severity—stages (0 to 5) and retinal localization—zones (I to III) [10]. The presence of plus disease, tortuosity and dilation of central retinal vessels is a crucial sign for deciding the need for treatment. Severe ROP with indications for treatment (Type 1 ROP) is defined as any stage of ROP in zone I, with plus disease; ROP stage 3 in zone I, without plus disease; ROP stage 2 or 3 in zone II, with plus disease. Severe ROP requiring frequent follow-up but not fulfilling treatment criteria (Type 2 ROP) is defined as ROP stage 1 or 2 in zone I, without plus disease and ROP stage 3 in zone II, without plus disease [9]. Laser photocoagulation, which destroys the peripheral avascular retina, releasing angiogenic factors, helps reverse pathological vaso-proliferation. Laser treatment is often performed under general anaesthesia, which can be challenging for these vulnerable infants. Potential side effects after laser treatment are retinal haemorrhage, visual field loss, myopia, and retinal detachment [11]. Intravitreal injection with anti-VEGF can be performed under sedation, thereby avoiding the risks associated with general anaesthesia. However, intravitreal anti-VEGF agents enter the bloodstream, suppressing VEGF over an extensive period (ranging from weeks to months) with potential long-term systemic effects [12].

Dexamethasone is a synthetic glucocorticoid with anti-inflammatory effects. It is widely used in adults to treat ocular surface and intraocular inflammation, as well as to manage complications from branch retinal vein occlusion and diabetic retinopathy [13, 14].

Research in both animals and infants has shown the involvement of inflammatory mediators in the development of ROP [15–19]. Dexamethasone eye drops are commonly used in preterm infants to reduce local inflammation after laser treatment for severe ROP. Öhnell et al., in a retrospective uncontrolled study, reported regression of severe ROP in infants following dexamethasone eye drops prior to planned laser treatment [20], and Yagi et al. observed comparable results in a pilot study [19]. If treatment with dexamethasone eye drops efficiently prevents the progression of ROP with less severe disease and fewer cases requiring treatment, infants may avoid general anaesthesia and retinal sequelae. However, no clinical trial has yet evaluated the efficacy and safety of administering dexamethasone eye drops to preterm infants with severe ROP. Topical administration of dexamethasone has been studied in a mouse model of ROP, oxygen-induced retinopathy (OIR), and when administered concurrently with oxygen exposure in OIR, a protective effect has been reported [17]. However, the timing of administration appears to be critical, as topical dexamethasone administered before the peak of neovascularization in OIR suppressed neovascularization by 30%, whereas later dexamethasone treatment had no effect [18]. In OIR, optimally timed topical dexamethasone administration and reduced neovascularization were associated with enhanced retinal mitochondrial function and decreased inflammatory response in immune cells [19]. Thus, research from OIR supports the clinically reported findings that topical dexamethasone may be an effective strategy to prevent severe ROP. Understanding the importance of timing in steroid treatment may explain previous conflicting results regarding intravenous and oral corticosteroids and ROP development [21, 22].

Studies on the efficacy and safety of dexamethasone eye drops to prevent severe ROP needing treatment in preterm infants are warranted. We designed a prospective, randomized, double-blinded, controlled, multi-centre intervention trial to include preterm infants with severe ROP not fulfilling treatment criteria, i.e. infants with Type 2 ROP and infants with stage 2 ROP in posterior zone II. We aim to reduce the number of infants with severe ROP needing treatment by 60% with the dexamethasone intervention compared to placebo.

## Methods/design

### Study design

The study is a national multi-centre, randomized, double-blinded, controlled prospective trial. The intervention group receives dexamethasone eye drops, 1 mg/ml (Dexafree®), while the control group receives placebo, saline (Drop-it®). The study consists of an intervention phase (main) study and an extension phase (follow-up) study. Figure 1 gives a schematic overview of the complete study schedule.

**Fig. 1 Fig1:**
[figure not shown]
Schematic overview of the complete study schedule

[name] ([contact]) is the primary sponsor and principal investigator (PI) in this study. The steering group is composed of three experienced paediatric ophthalmologists. The first infant was enrolled on 2022/09/22, and recruitment is ongoing.

### Inclusion and exclusion criteria

Infants are eligible if they fulfil the following criteria:Infants born with a gestational age (GA) < 30 weeks.ROP stage 1 or stage 2 without plus disease in zone I.ROP stage 2 or stage 3 in posterior zone II without plus disease, with or without notch in zone I.ROP severity must be documented using wide-field digital imaging system photography (RetCam), and eligibility must be confirmed by at least two of three experienced paediatric ophthalmologists in the steering group.Signed informed consent by the parents/guardians (oral and written information).

The exclusion criteria are:Ongoing ocular infection.If the neonatologist or ophthalmologist considers the infant unsuitable for the study.

### Eligibility, randomization and blinding

Infants evaluated for eligibility for enrollment in the study will be identified at routine ROP screening by the local ophthalmologist. ROP evaluations will adhere to clinical screening practice according to national guidelines. RetCam will be used at the ROP screening to document the extent of ROP disease, and images will be saved in the clinical record file. When the ROP screening ophthalmologist evaluates eligibility, the PI and the steering group will be contacted. Images will be evaluated, and eligibility for inclusion must be confirmed by at least two of three ophthalmologists in the steering group.

Parents/guardians will be given oral and written information about the study via the HOPE Parent Application (Addi Medical) and asked to participate if the infant is eligible. The signed informed consent will be collected before any study-specific data is reported and the infant is randomized. Randomization will be performed stratified by centre by a study nurse using an electronic application (HOPE). After randomization, the study nurse will provide eye drops to the assigned neonatal nurse in the neonatal intensive care unit (NICU) for administration or to the parents or guardians if the infant is discharged from the hospital. In case of problems regarding the study eye drops, a randomization list is safely stored in a locker at the NICU and available 24 h/day in case of emergency and safety issues. All investigators, ophthalmologists, staff, and patients/guardians, except pharmacists, are blind to the participants’ eye drop assignments. The single-dose containers for dexamethasone and placebo are similar, and identification of drop content will not be visible to an untrained eye.

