### Intervention

Study patients will be randomized to receive eyedrops with either dexamethasone 1 mg/ml (Dexafree®) in single-dose containers supplied by Thea Nordic or placebo, saline (Drop-it®) also in single-dose containers. Saline (Drop-it®) is a sterile, buffered saline without preservatives, with the same sodium chloride content as the tear film. The dose of dexamethasone has been adjusted to maintain efficacy while minimizing the medication dosage.

Based on the severity of ROP, the eye drops are administered at a dosage of one drop every other day to one drop daily in affected eyes, Table 1. The maximum intervention duration is 12 weeks. The dosage will be adjusted within the protocol’s range if ROP regresses or progresses. When discontinuing intervention, drops are tapered over one week; if the infant receives one drop daily, the dosage should be reduced to one drop every other day for one week before discontinuing intervention. After laser treatment, the infant will receive dexamethasone 1 mg/ml to reduce post-laser inflammation; the dose and duration will be determined by the ophthalmologist in charge, based on local routines. If anti-VEGF treatment is planned, all eye drops will be stopped immediately to reduce the risk of infection and endophthalmitis in cases of dexamethasone intervention. To reduce systemic absorption of the medication, we inform caregivers to tilt the baby's head to the left when the left eye is given a drop and to the right when the right eye is being dropped and instantly wipe off the excessive fluid with a soft compress. Intervention will be given at several weeks of age and during a limited period.

**Table 1 Tab1:** Administration schedule for eye drops according to ROP severity in affected eye/eyes

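### Emergency unblinding from a list kept on the NICU, and containers masked only against an untrained eye, put masking at avoidable risk

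*Protocol article*

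**What the plan says.** All from the protocol article.

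- **Code-break** (Eligibility, randomization and blinding): "a randomization list is safely stored in a locker at the NICU and available 24 h/day in case of emergency and safety issues". The sentence opens with problems concerning the study drops in general, so the occasions for access are not narrowly drawn.
- **Who is blind** (same section): "All investigators, ophthalmologists, staff, and patients/guardians, except pharmacists, are blind to the participants’ eye drop assignments".
- **Containers** (same section): "The single-dose containers for dexamethasone and placebo are similar, and identification of drop content will not be visible to an untrained eye". Under Intervention, the active arm is Dexafree in single-dose containers and the control is "placebo, saline (Drop-it®) also in single-dose containers", so these are two different commercial products.
- **Handling** (same section): a study nurse randomises in the HOPE application, stratified by centre. Then "the study nurse will provide eye drops to the assigned neonatal nurse in the neonatal intensive care unit (NICU) for administration", or the drops go to the parents if the infant has been discharged.
- **Endpoint and image reading**: the primary outcome is progression to Type 1 ROP. Under Inclusion and exclusion criteria, entry images are read centrally: "eligibility must be confirmed by at least two of three experienced paediatric ophthalmologists in the steering group".

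**The concern.** A double-blind trial needs a round-the-clock code-break, and having one is not a fault. The form and place of this one are the difficulty. A list may unmask infants other than the one in trouble, and it is kept where the drops are given. The container wording adds a second weakness, because it gives no assurance about trained staff, who make up most of the people declared blind.

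At stake is the even-handedness of endpoint calls. Type 1 ROP is defined by explicit criteria, but one of them, plus disease, is a grading of how tortuous and dilated the central vessels are. If knowledge of the arm reached those who grade or influence that sign, borderline calls could drift in one direction.

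**Working it through.** **1. Single code against list.** A single-infant code-break reveals one allocation. A list of k infants can reveal up to k, so up to k − 1 infants are unmasked without need. The article does not give k. It does not say whether the list covers one centre or several, only infants already randomised or future slots too, or whether entries are sealed. The only ceiling in the text is the planned total of 100. Any k of 2 or more is worse than a single code, and HOPE already performs the randomisation electronically.

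**2. Blinding claimed against blinding supported.**

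| | Article states |
|---|---|
| Claim | everyone except pharmacists is blind, including staff and ophthalmologists |
| Measure | containers similar; content not apparent to someone untrained |
| Handlers described | study nurse, neonatal nurse, parents |

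Two of the three handlers are health professionals. The Background says dexamethasone drops are in common use in preterm infants after laser, so some staff may know what such containers look like. The measure therefore supports less than the claim.

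**3. Does the endpoint depend on a graded sign?** The entry categories are set against the Type 1 definition in the footnote to Table 1.

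| Entry category (all without plus disease) | Routes to Type 1 |
|---|---|
| Stage 1 or 2, zone I | plus disease, or stage 3 in zone I |
| Stage 2, posterior zone II | plus disease, while disease stays in zone II |
| Stage 3, posterior zone II | plus disease, while disease stays in zone II |

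Plus disease is a route for every entry category and the only one for disease that stays in zone II. The article does not give the expected split between zones.

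**4. How much tolerance the design has.** The planned size reproduces. For 50% against 20%, with a two-sided Fisher test at 0.05 and 45 per arm, exact power is 81.5%, and 45 / 0.9 = 50 per arm, or 100 in total.

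Now assume no true effect, with 50% in both arms. Suppose a share b of placebo non-progressors is called Type 1, and the same share b of dexamethasone progressors is not. The observed rates become 0.5 + 0.5b and 0.5 − 0.5b, and 45 × 0.5 × b infants per arm are shifted.

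| b (assumed) | Rates | Infants shifted per arm | Chance of a significant result for dexamethasone |
|---|---|---|---|
| 0 | 50.0% / 50.0% | 0 | 1.3% |
| 5% | 52.5% / 47.5% | 1.1 | 4.1% |
| 10% | 55.0% / 45.0% | 2.25 | 10.3% |
| 15% | 57.5% / 42.5% | 3.4 | 21.5% |
| 20% | 60.0% / 40.0% | 4.5 | 37.9% |

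This uses Fisher's test, as in the sample size section, not the adjusted logistic regression planned for the analysis. Every b above zero is an assumption. The table shows sensitivity to biased calls and does not estimate any bias in this trial.

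**The case against.** The strongest reply is that the article already contains real safeguards. Allocation runs through an electronic application, consent comes before randomisation, and eligibility is confirmed by the steering group. The list is described as safely stored and reserved for emergencies and safety. Ophthalmologists are declared blind, and none is described as handling the drops. The article condenses a longer document (Table 2 cites version 4 of the study protocol), where access logs, labelling and endpoint reading may be set out.

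Most of this stands, and it rules out several stronger readings that a reader might infer:

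- **That the complete list sits in every NICU.** The text speaks of a list at the NICU and does not give its scope.
- **That concealment is broken.** This would need a list showing future allocations, recruiting staff able to reach it, and room to steer enrolment despite steering-group confirmation. None of these is documented.
- **That ophthalmologists recognise the drops.** No section places the containers in front of the assessor.
- **That Type 1 calls go unconfirmed.** Central reading is stated for entry only, but silence about the endpoint in a condensed article is not evidence that it is absent.
- **That the endpoint is wholly subjective.** It has written criteria, and stage 3 in zone I qualifies without plus disease.

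The reply does not remove what the article states: a list as the code-break, its location on the ward, and a masking assurance limited to the untrained. These are stated choices, not details left to another document.

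**Conclusion.** The point holds as an avoidable risk to masking. One opening of the NICU list could reveal the arm of more than one infant, and future allocations too if the list shows them. The container wording supports less blinding than the article claims. The consequence matters because plus disease, a graded sign, is a route to the primary endpoint for all entry categories and the only one for disease that stays in zone II.

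The size cannot be derived from the article, because the list's scope, the number of openings and any effect on grading are not given. The conclusion assumes that the list covers more than one infant, and that some staff who handle the containers could tell the products apart. It is a worthwhile improvement and does not show that the trial's result is compromised.

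**What to change.** 1. Remove the list from the NICU and hold it only with the pharmacists, who are already unblinded.
2. Keep 24-hour emergency access through single-infant code-breaks, either in HOPE with an audit trail or in sealed numbered envelopes.
3. Have the pharmacy over-label or sleeve both single-dose containers identically, and replace the untrained-eye wording with a description of that measure.
4. Optionally, for the analysis only and without delaying care, apply the two-of-three steering-group reading, masked to arm, to Type 1 calls, using RetCam images from the screening visits.

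The cost is a system setting or a set of envelopes, plus labelling work. The optional step adds reading time for ophthalmologists already in place. The article reports recruitment as ongoing, so steps 1 to 3 can protect infants still to be enrolled, and saved images would allow step 4 for those already in the trial. If the full protocol already provides any of this, correcting the article's description is enough for that item.

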### Intervention

Study patients will be randomized to receive eyedrops with either dexamethasone 1 mg/ml (Dexafree®) in single-dose containers supplied by Thea Nordic or placebo, saline (Drop-it®) also in single-dose containers. Saline (Drop-it®) is a sterile, buffered saline without preservatives, with the same sodium chloride content as the tear film. The dose of dexamethasone has been adjusted to maintain efficacy while minimizing the medication dosage.

Based on the severity of ROP, the eye drops are administered at a dosage of one drop every other day to one drop daily in affected eyes, Table 1. The maximum intervention duration is 12 weeks. The dosage will be adjusted within the protocol’s range if ROP regresses or progresses. When discontinuing intervention, drops are tapered over one week; if the infant receives one drop daily, the dosage should be reduced to one drop every other day for one week before discontinuing intervention. After laser treatment, the infant will receive dexamethasone 1 mg/ml to reduce post-laser inflammation; the dose and duration will be determined by the ophthalmologist in charge, based on local routines. If anti-VEGF treatment is planned, all eye drops will be stopped immediately to reduce the risk of infection and endophthalmitis in cases of dexamethasone intervention. To reduce systemic absorption of the medication, we inform caregivers to tilt the baby's head to the left when the left eye is given a drop and to the right when the right eye is being dropped and instantly wipe off the excessive fluid with a soft compress. Intervention will be given at several weeks of age and during a limited period.

**Table 1 Tab1:** Administration schedule for eye drops according to ROP severity in affected eye/eyes

	**Number of drops per day**
ROP stage 1–2 without plus disease in zone I	1 drop every other day
ROP stage 2 without plus disease in posterior Zone II	1 drop every other day
ROP stage 3 without plus disease in zone II, with or without notch in zone 1	1 drop daily
Type 1 ROP* fulfilling treatment criteria	If anti-VEGF injection is planned, eye drops should be immediately withdrawn
ROP treatment and post treatment	Routines at the clinic

*Abbreviations:*
*ROP* Retinopathy of prematurity, *VEGF* Vascular endothelial growth factor

*Any stage of ROP in zone I, with plus disease; ROP stage 3 in zone I, without plus disease or ROP stage 2 or 3 in zone II, with plus disease

The parents/guardians will record doses provided to the infant at home in the HOPE parent application. The total number of single doses used, along with compliance, will be estimated by collecting information about the number of doses returned and recorded in the HOPE application.

